### Interim analyses {21b}

No interim analyses will be conducted during the intervention sessions, which are only 4 weeks long. Additionally, we do not anticipate systematic harm to participants due to study participation, thus we do not have study stopping guidelines in place. For individual participants who clinical supervisors deem as having serious risk of harm to self or others, the local expert clinician could decide, in collaboration with the school administration, to withdraw the participant from the trial and instead provide more intensive individual support. See supplemental emergency protocol documents for more. However, the outcomes from 2-week midpoint, 4-week endpoint, and 1-month follow-up will most likely be analyzed prior to those at 3-month, 6-month, and 9-month follow-up, and will accordingly be reported separately. This is because of the large number of groups and outcomes, which would likely prohibit reporting all in one manuscript.

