This past work may raise questions about whether the promising effects of the Shamiri intervention are due to the “bundling” together of three-character strength interventions, or whether some character strength interventions are more helpful than others, or even potentially beneficial when used alone. Answering these questions may shed light on the mechanisms and outcomes targeted by each individual intervention, as well as helping prioritize which mental health interventions are most important to disseminate. Previously, we investigated the effects of each element of the Shamiri intervention in a universal, classroom-based microtrial with 2-week follow-up [34]. This trial provided some initial evidence that the value affirmation and growth mindset components may be more effective on their own than the gratitude component, particularly for reducing symptoms of anxiety [34]. However, this trial had several limitations: first, it did not allow for comparison between the individual elements and the three-component Shamiri; second, the trial was cluster-randomized, and therefore underpowered to detect small effects; and third, microtrials are not intended to assess long-term effects. Thus, to build on our existing work, we plan to conduct a large, well-powered randomized controlled trial to compare the longer-term follow-up effects of the combined Shamiri intervention and its constituent character strength interventions (i.e., growth mindset, gratitude, and values), against an active control group.

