### Sample size {14}

We conducted a power analysis using Optimal Design, a statistical simulation software which can estimate sample size for randomized controlled trials assessed using multi-level (i.e., mixed effects) models [74]. In Optimal Design, we estimated the required sample size for a person-randomized trial with six-time repeated measures (baseline, midpoint, post, 1-month follow-up, 3-month follow-up, 6-month follow-up, and 9-month follow-up). Additionally, for each outcome measure, we have four contrasts of primary interest (each intervention condition compared to the control), thus, using a conservative *p* value correction, we would divide the typical alpha value of .05 by four and get a *p* value threshold for significance of .0125. Finally, we assumed that we are interested in detecting a minimum post-treatment effect size of .3. We selected this value for the following reasons: 1) it is slightly lower than the effect sizes found in most previous trials of Shamiri, which range from .32–.83 at the latest follow-up points [3, 20, 33, 34], which will allow us to detect potentially smaller effects of the individual component interventions, and to detect effects in a universal sample, and 2) a standardized effects size of .3, which is considered small to medium, remains clinically meaningful and important in our view, whereas a change smaller than that may not be as clinically meaningful. Given these parameters, we found that a sample of 515 students would be needed to conduct a two-group trial with a power of .80. So, for this five-group trial, we multiplied that by 2.5, to get a final target sample size of 1288 students. Because in a past trial with 7-month follow-up there was a high dropout rate during follow-up of up to 40% [33], we will initially invite 2147 students to the sessions, assuming that around 40% of them will drop out prior to the sessions or during the follow-up period.

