Primary models will include all five groups, using the control group as the contrast group. Secondary models will include the four intervention conditions, using the full Shamiri intervention as the contrast group. Significant (*p* < .05 with a Holm-Bonferroni correction to account for four comparisons within each model) time × condition interactions will indicate that one condition produced significantly steeper improvements than another condition across the time included in the analyses. As described above and per recommendations outlined in past literature [78], the Holm-Bonferroni correction will be applied at a family-wise level (i.e., to account for multiple group comparisons on each outcome), rather than at a study-wise level.

Additionally, for all pairwise contrasts (including those comparing active interventions to each other) on all primary and secondary outcomes, effect sizes will be calculated as mean gain scores, to compare change within the various intervention and control groups.

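### Neither the report to 1 month nor the later report is named as the primary test; if each uses Holm at the full .05, the false-claim risk per questionnaire outcome is about .06 to .085

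*Protocol article*

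**What the plan says.** Sample size {14} defines the contrasts: "for each outcome measure, we have four contrasts of primary interest (each intervention condition compared to the control". It sets a planning threshold of .0125 for each. Its repeated-measures calculation lists occasions out to 9 months.

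Statistical methods {20a} tests the time × condition interaction at .05 "with a Holm-Bonferroni correction to account for four comparisons within each model". It describes the correction as acting at a family-wise level, "to account for multiple group comparisons on each outcome), rather than at a study-wise level". A significant interaction is read as "significantly steeper improvements than another condition across the time included in the analyses", so the meaning of the test depends on which visits are in the model.

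Interim analyses {21b} then states that "the outcomes from 2-week midpoint, 4-week endpoint, and 1-month follow-up will most likely be analyzed prior to those at 3-month, 6-month, and 9-month follow-up", and that these results "will accordingly be reported separately". The reason given is the number of groups and outcomes, too many for one manuscript.

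Objectives {7} hypothesises that every intervention arm will beat the control on each primary outcome and names no time point. Background and rationale {6a} says the trial is planned "to compare the longer-term follow-up effects of the combined Shamiri intervention" and its components.

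**The concern.** The family of tests is described by outcome, but the correction works by model. These amount to the same thing only if each outcome has one primary model. With two separately reported windows there would be two sets of four control contrasts on the same questionnaire, and the article neither divides alpha between them nor says which set tests the hypothesis.

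Two things are at stake. First, an arm could be declared better than control on the strength of either window, so the chance of a false claim on an outcome is higher than a single Holm family allows. Second, because the test is defined by whatever time is included, the window that counts as primary could be settled after the 1-month results have been seen.

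**Working it through.** **Inputs from the article.** Alpha .05 with Holm over four comparisons in each model ({20a}); four contrasts against one control ({14}); equal allocation to five arms ({8}); an early window (2 weeks, 4 weeks, 1 month) and a later one (3, 6, 9 months) ({21b}).

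**Assumptions.** Two-sided tests (not stated); the full .05 in each report (inferred from the per-model correction and the absence of a split); correlation between the early and later test statistics of 0 to .9 (not in the article).

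**Step 1: the plan's own figure.** .05 / 4 = .0125, as stated in {14}. The two-sided critical value is |z| > 2.498.

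**Step 2: one window.** With equal arms, two contrasts that share the control have correlation .5. If no arm differs from control, Holm rejects something exactly when the smallest of the four p-values is at or below .0125. Simulation (1,000,000 draws) gives .043. Holm therefore holds inside a single model.

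**Step 3: either of two windows.** Same simulation, with the arm-level statistics of the two windows correlated at r:

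| r | At least one false claim in either report |
|---|---|
| 0 | .085 |
| .5 | .080 |
| .8 | .070 |
| .9 | .063 |
| 1 | .043 |

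Check at r = 0: 1 − (1 − .0432)² = 1 − .9155 = .0845, in line with the simulated .085. The figure returns to .043 only if the two windows give identical statistics.

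**Step 4: what correlation is plausible.** I took visits at 0, 0.5, 1, 2, 4, 7 and 10 months from baseline, or as equally spaced waves, and compared linear slopes. Random-slope variance ran from 0 to .05 of the residual variance.

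- Early slope against a slope through all visits: r of .16 to .59, risk .084 to .078.
- Early slope against a slope through baseline and the late visits only: r of .42 to .67, risk .081 to .076.

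So the answer is close to .08 whether or not the later model refits the early data.

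**Step 5: which outcomes.** PHQ-8, GAD-7 and SWEMWBS are collected on the visit schedule and fit the two windows. Academic performance is collected for the terms before, during and after the intervention (Outcomes {12}; Fig. 1 note), so the two windows do not map clearly onto it.

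**The case against.** The strongest reply is that the article promises only to correct for comparisons among groups, and does so within a model. Holm delivers that. Results at 1 month and at 9 months can be seen as different questions, and correcting across them is a choice of family. The separate reporting is only described as most likely, and {21b} mentions neither models nor alpha. An analysis plan that is not shown may settle the matter.

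Much of this stands. The split is expected but not fixed, and the full .05 per report is inferred. A reader might infer that the plan breaks an explicit guarantee of error control. The text does not go that far, because its family is worded both by model and by outcome. Treating the windows as separate questions would be defensible if the article said so and named the one that carries the hypothesis. It does neither, and that goes beyond leaving detail to another document: the stated family, the stated test and the stated reporting sequence do not fit together.

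Three other readings are tempting and not supported:

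- **That the early window lacks power.** {14} sizes the trial for a post-treatment effect of .3 and allows for 40% dropout before the sessions or during follow-up. No power for the shorter window is given, so no shortfall is shown.
- **That all four primary outcomes are affected.** Term grades do not clearly fit.
- **That this is an early-stopping problem.** No stopping rule or design decision depends on the early analysis.

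**Conclusion.** The point holds in conditional form. If the data to 1 month and the later data are reported separately and each report uses Holm at .05, the chance of at least one false claim on a given questionnaire outcome is about .06 to .085, against .043 for one window. With correlations suggested by the visit schedule it is .076 to .084. This rests on two-sided tests, no true difference in any arm, and a between-window correlation that the article does not give.

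The inflation is moderate. It is counted within one outcome only and asks for no study-wise control, which the article openly declines. The open choice of window matters at least as much as the figure: as written, the choice can follow the 1-month results. The change should be made.

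**What to change.** Before any outcome data exist, name one confirmatory time window for each of PHQ-8, GAD-7 and SWEMWBS. Under Trial status the article says recruitment had not begun at this version, so the choice could still be made blind to results. The model using all occasions to 9 months is the natural candidate: it matches the longer-term aim in {6a} and the repeated-measures calculation in {14}. Label the other report secondary, and state in {20a} that the Holm family is the four control contrasts in the named model. With one confirmatory window the risk per outcome is .043. For grades, state separately which terms enter the primary comparison.

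The cost is protocol wording, and an early paper that can present short-term results but carries no confirmatory claim.

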### Methods for additional analyses (e.g., subgroup analyses) {20b}

As part of our main analyses, we do not plan to carry our additional subgroup or adjusted analyses. However, we plan to conduct exploratory analyses such as moderator and mediator analyses and epidemiological analyses using the trial data. Such analyses will be published separately from the main analyses of primary and secondary trial outcomes.

### Methods in analysis to handle protocol non-adherence and any statistical methods to handle missing data {20c}

Missing item and subject-level data will be imputed at least five times using Fully Conditional Specification (FCS), implemented using the multivariate imputation by chained equations (mice) package in R [79]. Multi-level models will be built using the pooled imputed datasets. Additionally, as appropriate, we may report results using the un-imputed dataset or conduct other sensitivity analyses using different styles of data imputation or using last observation carried forward. As described further under Strategies to Improve Adherence to Interventions, a selection of session recordings will be rated by independent raters for fidelity, and results of these ratings will be reported. If the study team or independent raters identify systematic deviations from the protocol by certain lay providers, students who received counseling from these lay providers may be removed from the dataset for sensitivity analyses.

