### Plans to promote participant retention and complete follow-up {18b}

Study team members will work with school officials to promote participant retention. School officials will help the study team remind participating students to attend intervention sessions at the scheduled times and attend follow-up data collection sessions. The study team will also conduct raffles of small prizes (e.g., water bottles and t-shirts) for participants during intervention sessions and provide a small gift to each school (in the form of an in-kind donation of materials including some to prevent the spread of COVID-19).

Participants who miss any intervention session(s), with the exception of the first which includes essential baseline data collection, will not be removed from the study nor barred from attending subsequent sessions. The study team will continue to collect measures completed by such participants during any sessions and follow-up points they attend; of course, participants can stop attending sessions at any time and for any reason. Because school grades are publicly accessible via participating schools, we will still collect school grades for any participant who discontinues or is removed from the intervention after the first session for any reason listed under {11b}, unless the participant explicitly withdraws consent to participate in the study, in which case their data will be removed from all analyses.

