## Statistical methods

### Statistical methods for primary and secondary outcomes {20a}

Outcome measures will only be analyzed if they demonstrate internal consistency within the full sample at baseline, defined as an alpha value of .70 or above [75]. For those outcome measures that pass this threshold, all main analyses of primary and secondary outcomes will follow an intent-to-treat approach, meaning that all participants who consent, are randomized into the groups, and complete baseline measures will be included in all analyses (see 20c below for more about plans for handling missing data).

For all analyses of primary and secondary outcomes, we plan to use linear mixed effects models to model time × condition interaction with a random intercept for participant ID to allow for individual variation at baseline. We plan to control for age and sex in all models of primary and secondary outcomes. Age will be included because older adolescents report increased psychosocial stress and thus greater risk of mental illness [3]. Similarly, sex differences in anxiety and depression are widely documented in adolescents including Kenyan adolescents [3, 76]. Additionally, the authors will test more complicated random effects structures which reflect the hierarchical structure of the data, including random effects for groups within group leaders, crossed random effects for schools and group leaders, and for participants in groups. We will also test adding a random slope for participant ID and for school; however, these added random effects may result in overfitting, which would reduce the generalizability of our findings. If this is the case, we will select a more parsimonious model with a simpler random effects structure. These variables (group leader, school, and group) will also be tested as covariates rather than random effects in the model, and final model selection will be done taking into account both overfitting warnings and Akaike Information Criterion (AIC) [77].

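### With about 40% loss expected, the main imputation can credit students who stop attending with their arm's benefit, and the optional checks named, including last observation carried forward, do not test this well

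*Protocol article*

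**What the plan says.** The protocol article's section on non-adherence and missing data {20c} states: "Missing item and subject-level data will be imputed at least five times using Fully Conditional Specification (FCS". The multi-level models are then built on the imputed datasets. The further checks are optional: "we may report results using the un-imputed dataset or conduct other sensitivity analyses using different styles of data imputation or using last observation carried forward".

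Four other places bear on this:

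- Statistical methods {20a}: "all main analyses of primary and secondary outcomes will follow an intent-to-treat approach". The set is defined so that "all participants who consent, are randomized into the groups, and complete baseline measures will be included in all analyses".
- Sample size {14}: 2147 students are invited, "assuming that around 40% of them will drop out prior to the sessions or during the follow-up period". The 40% is taken from follow-up loss in a past trial. The split between loss before the sessions and loss during follow-up is not given.
- Retention {18b}: students who miss a session other than the first stay in the study, and "The study team will continue to collect measures completed by such participants during any sessions and follow-up points they attend". Grades are still collected after a student discontinues, unless consent is withdrawn.
- Background {6a}: the aim is to "compare the longer-term follow-up effects of the combined Shamiri intervention and its constituent character strength interventions". The trial design section {8} follows students to 9 months.

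**The concern.** Standard chained-equations imputation fills a missing score from students who look alike on the variables in the model. If that model holds arm and earlier scores but not attendance, a student who stopped coming after one session is filled in like an arm-mate who completed four. The estimate then drifts towards the effect had everyone kept attending, which differs from the intent-to-treat effect promised in {20a}.

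Leaving sessions and missing outcomes are likely to be linked early on. The participant timeline {13} has midpoint forms completed straight after a session, and section {18a} has lay providers administer the midpoint and endpoint forms. Section {21b} says that results up to 1 month will most likely be reported first.

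The size matters because the sample size section treats .3 as the smallest effect of interest and doubts the clinical meaning of anything smaller. A true .24 could be reported as about .30. Contrasts of single elements with full Shamiri would also shift if drop-off differed by arm.

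**Working it through.** **The plan's own figures.** A two-group comparison with effect .3, two-sided alpha .0125 (two-sided is assumed) and power .80 needs 250 per arm by the noncentral t, 500 in all. The stated 515 is within 3% and gives power of about .815. Then 515 × 2.5 = 1287.5, rounded to 1288, and 1288/(1 - .40) = 2147. These reproduce, so .3 and 40% are used below.

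**Leavers and the imputation.** Assumptions not in the documents: the effect at 9 months is .30 SD in students who stay and zero in leavers, 40% of 9-month scores are missing, and arm is in the imputation model. Let q be the share of analysed students who leave the sessions.

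- True intent-to-treat effect = .30(1 - q).
- If no leaver returns, imputation gives about .30, so the excess is q/(1 - q).
- If a share r of leavers returns and total loss stays at 40%, leavers are rq/.60 of the observed scores. Imputation without attendance gives about .30(1 - rq/.60).

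Simulated values are in brackets (two arms of 429, 150 runs, visit correlation .6, ANCOVA effect at 9 months).

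| q | True | Imputed, none return | Excess by formula | Imputed, r = .30 | Excess by formula | Attendance × arm added, r = .30 | Control-based, none return |
|---|---|---|---|---|---|---|---|
| .10 | .27 | .30 (.311) | 11% | .285 (.281) | 6% (4%) | (.266) | (.277) |
| .20 | .24 | .30 (.307) | 25% | .270 (.269) | 12.5% (12%) | (.238) | (.243) |
| .30 | .21 | .30 (.288) | 43% | .255 (.255) | 21% (21%) | (.209) | (.201) |

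A separate large simulation (20,000 per arm; effect .45 at week 4 and .30 at month 9; arm in the model) gave:

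- Loss unrelated to leaving sessions: truth .292, imputed .293. No bias.
- Half of the missing are leavers, none return: truth .243, imputed .306.
- The same, but half of the leavers return: truth .243, imputed .265 without attendance and .243 with attendance and its interaction with arm.
- All of the missing are leavers, none return: truth .176, imputed .296.

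Attendance can help only if some leavers return. If none do, no data inform its coefficient, and only an analysis that departs from missing at random can show how much the result depends on the assumption.

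**Last observation carried forward.** Suppose all 40% are lost after week 4, with effect e4 at week 4 and e9 at month 9. The method gives .60·e9 + .40·e4.

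- e4 = .45, e9 = .30: .18 + .18 = .36, which is 20% too high (simulated .356 against .292).
- e4 = .60, e9 = .30: .18 + .24 = .42, which is 40% too high.
- e4 = e9 = .30: .30, correct.
- With losses spread over follow-up, simulation gave .161 against .10 when an effect of .30 fades to .10, and .242 against .30 when the effect grows to .30.

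**The un-imputed dataset.** A likelihood-based mixed model on the observed scores also assumes missing at random, so it cannot test that assumption.

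**The case against.** The other side has real force.

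- Students who never attend are probably outside the analysis. Section {18b} excepts the first session from its promise to keep students who miss sessions, and the timeline places the remaining baseline measures just before it. So q should be read as students who stop after the first session.
- The 40% comes from follow-up loss in an earlier trial. Students lost after the four-week course were treated, and if their loss is unrelated to leaving sessions the imputation is unbiased.
- Later follow-ups run through school officials {18a}, apart from the groups, so some leavers will be measured. With 30% returning, the excess at q = .10 falls to about 4% to 6%. Zero benefit is also a harsh assumption for a student who attended three sessions. Grades are less affected.
- The article does not describe the imputation model, and an analysis plan may properly do so. If arm were left out, the bias would usually run towards zero: .253 against .301 with no leavers, and .210 against .235 with leavers as half of the missing.
- Last observation carried forward is optional and not always worse. When all of the missing were unmeasured leavers, who carried baseline values, it gave .173 against .176.

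All of this stands and limits the size. It does not supply a check. That last agreement comes from assuming no benefit in students last seen at baseline. It fails for those last seen at or after week 4 if effects change.

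Three stronger readings are tempting but unsupported. A reader might infer that last observation carried forward is the only alternative named, yet the same sentence names the un-imputed dataset and other imputation styles. A reader might infer that no named method can estimate the intent-to-treat effect, yet imputation does so when loss is unrelated to leaving, or when attendance is modelled and leavers are remeasured. And a reader might take the whole 40% as untreated students credited with benefit, which the documents do not say.

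**Conclusion.** The point holds in conditional form. The main analysis rests on missing at random at an expected loss of about 40%, and it can overstate the intent-to-treat effect on the questionnaire outcomes if some students stop attending after the first session and give no later form. The excess is about q/(1 - q) if none return and they gain nothing, less if some return, and nil if loss is unrelated to leaving sessions. The documents do not fix q, so .10 to .30 is an illustrative range. The direction depends on arm being in the imputation model.

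The calculations concern the difference at 9 months. The planned test is a time × condition interaction, for which the size was not computed.

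The named checks do not settle the matter: one shares the assumption, one is unspecific, and last observation carried forward assumes persistence, which is part of what the longer-term aim asks. This does not invalidate the plan. A better method than the one named is available at little cost and should be adopted.

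**What to change.** In section {20c}:

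1. Keep multiple imputation as the main method. State that the imputation model includes arm, number of sessions attended and their interaction, so that leavers who return for follow-up forms inform the imputation of those who do not.
2. Replace last observation carried forward as the named sensitivity analysis with one fixed missing-not-at-random analysis for each primary questionnaire outcome (PHQ-8, GAD-7, SWEMWBS). Use either control-based imputation for students who stopped attending, or a delta shift increased in steps until the conclusion changes. Report it beside the main result.

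The cost is a wording change, a little more code around the imputation package already chosen, and session attendance kept as an analysis variable. No extra students are needed. The sensitivity estimates will be somewhat smaller and less precise.

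### The imputation in {20c} gives the delivery group no place; if run single-level, standard errors for late follow-up contrasts would be about 3–15% too small at a group ICC of .02–.10

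*Protocol article*

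**What the plan says.** Protocol article, {20c}: "Missing item and subject-level data will be imputed at least five times using Fully Conditional Specification (FCS". The software named is mice. The order of steps is fixed: "Multi-level models will be built using the pooled imputed datasets". Analysis without imputation is optional: "we may report results using the un-imputed dataset or conduct other sensitivity analyses".

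Protocol article, {20a}: the base model is a linear mixed model "with a random intercept for participant ID to allow for individual variation at baseline". The authors will also test "random effects structures which reflect the hierarchical structure of the data". The candidates listed are effects for delivery groups nested in leaders, for schools crossed with leaders, and for students within their groups. These terms may be dropped for overfitting or on AIC. Everyone randomized with baseline measures stays in all analyses, so missed later visits have to be filled in.

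Other relevant places:
- Trial design {8}: groups of 8–15 students share one lay provider over four weekly sessions, with follow-up to 9 months.
- Sample size {14}: dropout of up to 40% in a past trial, and about 40% planned for here, counting losses before the sessions.
- {18b}: grades are still obtained from schools after a student discontinues.

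**The concern.** An imputation model should carry at least the structure that the analysis model will estimate. Single-level chained equations draw each missing score from the student's own predictors, with errors independent across students. Two imputed scores in the same group then share nothing beyond those predictors, and neither do an imputed and an observed score. The completed data show too little between-group variance. A group random effect fitted afterwards estimates that diluted variance and cannot restore what the imputation left out.

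The contrasts most exposed are those at late follow-up, where most whole-visit imputation would fall. Longer-term effects are a stated reason for the trial (Background {6a}). Standard errors that are too small there would raise the type I error of the comparisons with control.

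**Working it through.** **The plan's own figures.** 515 × 2.5 = 1287.5, rounded to 1288. Then 1288 / (1 − .40) = 2146.7, rounded to 2147. Both agree with {14}. Per arm, 2147 / 5 ≈ 429, or about 36 groups of 12 (432 students).

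**Assumed, because the article does not give them.** Group ICC of 0, .02, .05 or .10; equal groups of 12; up to 40% of the last outcome missing. After adjustment for baseline, simulated complete data gave ICCs ρ of .027, .066 and .131 for the three non-zero values.

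**Step 1: dilution.** Two students in a group keep their shared component only if both are observed, so the completed-data ICC is about ρ* = (1 − f)²ρ, where f is the fraction missing. At f = .40 the factor is .36:
- .027 × .36 = .010
- .066 × .36 = .024
- .131 × .36 = .047

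Simulation gave .012, .024 and .048.

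**Step 2: standard error of one arm mean.** Residual variance is 1, k = 36 groups, N = 432. Observed: 432 × .6 = 259.2. Missing: 172.8. Many imputations are assumed.
- True variance: V = ρ/k + (1 − ρ)/259.2
- Within-imputation variance: W = ρ*/k + (1 − ρ*)/432
- Between-imputation variance: B = f²(1/259.2 + 1/172.8) = .16 × .009645 = .001543
- Ratio of reported to true SE: √[(W + B)/V]

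| Assumed ICC | ρ | V | W + B | SE ratio |
|---|---|---|---|---|
| 0 | 0 | .003858 | .003858 | 1.00 |
| .02 | .027 | .004504 | .004106 | 0.955 |
| .05 | .066 | .005437 | .004463 | 0.906 |
| .10 | .131 | .006992 | .005059 | 0.851 |

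**Step 3: simulation.** One contrast with no true effect, a group random effect always fitted in the analysis, data missing completely at random, single-level imputation pooled by Rubin's rules. Ratio of pooled SE to true SD:

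| Setting | ICC .02 | .05 | .10 |
|---|---|---|---|
| 40% missing, 5 imputations | 0.95 | 0.90 | 0.85 |
| 40% missing, post-treatment score also a predictor | 0.97 | 0.94 | 0.90 |
| 20% missing, 5 imputations | 0.985 | 0.945 | 0.87 |

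At ICC 0 the first setting gave 1.02, so no shortfall. With 20 imputations at ICC .10 and 40% missing the ratio was 0.81, the largest shortfall seen; Step 2 suggests about 0.85 there. Two further simulations gave similar ratios. One, with 20% lost by week 4 and 40% by 9 months, gave 0.97, 0.92 and 0.86. The other, with 5 imputations and 20%/40% missing, gave 0.94, 0.88 and 0.84.

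**Type I error.** At the .0125 threshold in {14}, the first setting gave .012, .014, .022 and .029 for ICC 0, .02, .05 and .10 (3000 runs; Monte Carlo error √(.0125 × .9875/3000) ≈ .002).

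**With a group effect in the imputation.** At 40% missing and 5 imputations the SE ratio was 0.97 at ICC .05 and 1.02 at ICC .10. Type I error was about .050 at nominal .05 and .017 at nominal .0125 (1200 runs; Monte Carlo error about .003).

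**The case against.** The strongest reply is that the article nowhere says the imputation is single-level. FCS is a framework, mice offers two-level methods, and the reference to item and subject level can be read as describing what is missing rather than the level at which the model works. Predictors and cluster terms are often left to an analysis plan, and none is shown. This stands: a reader might infer that the protocol has chosen an imputation that ignores groups, and the text does not support that. What remains is that {20c} does fix the method, the package, the minimum number of imputations and the order of steps, and the ordinary form of what it fixes omits a level that {20a} recognises.

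A reader might also infer that about 40% of all data will be imputed. The documents do not support that. The 40% is an upper figure from a past trial, and as planned here it includes students lost before the sessions, many of whom would not be in the analysis set. Earlier visits should be more complete, and grades come from school records.

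The group, leader and school terms are only to be tested. If they are dropped, clustering is ignored in the analysis whatever the imputation does; that is a separate problem.

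The size rests on an assumed ICC and on a single late contrast, not the full time × condition test over all visits. At ICC .02 the excess type I error is within simulation error, and at .05 the rate of .022 at nominal .0125 is not far above the .017 seen with the group effect in the imputation.

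Finally, making the un-imputed mixed model primary would be a trade-off between two approaches valid under missing at random, since imputation handles missing items and uses auxiliary variables. It is not asked for here.

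**Conclusion.** The point holds conditionally. If the imputation is run single-level and the group ICC is above zero, standard errors for late follow-up contrasts on the questionnaire outcomes are too small, even with a group random effect in the analysis. For an assumed ICC of .02 to .10 and 40% missing at the latest visits, the shortfall is about 3–15%, with one simulated setting near 19%. It shrinks when less is missing or earlier scores are predictors, and vanishes at ICC 0. Type I error rises moderately at ICC .05 and above, to about .02–.03 at nominal .0125 with 40% missing and baseline as the only earlier score in the imputation. The documents do not support saying that type I error is inflated without these conditions. The change is worth making before analysis because it is cheap and the affected contrasts matter to the trial's purpose.

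**What to change.** In {20c}, state that:

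1. Whole missing visits are imputed by two-level FCS (the 2l methods in mice), with delivery group as the cluster and with arm, baseline and earlier scores in the model, so that the imputation matches the group terms in the analysis model.
2. Single-level imputation is kept only for a few missing items within an otherwise completed scale.
3. The mixed model on all observed data will be reported as a sensitivity analysis, replacing "we may report results using the un-imputed dataset" with a commitment.

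The cost is a few sentences, a different call in the package already named, somewhat more analysis work and slightly wider intervals.
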